### Secondary outcome analyses

Because empirical evidence on the comparative efficacy and utility of both intervention formats under investigation is scarce, we will conduct a variety of explorative analyses on secondary outcomes. We will analyze improvements in perceived stress at an individual level in both study groups, by examining the number of participants who exhibit “reliable improvement”, employing the reliable change index (RCI) proposed by Jacobson and Truax in 1991. Participants will be defined as reliably improved if their PSS-10-score declines, from T1 to T3, with a reliable change index greater than 1.96, which equals 5.8 points on the PSS-10, based on an SD_post_ = 6.3 [50] and Mc Donald’s ω = .89 [51]. Response rates will be analyzed using the Pearson χ2 statistic.

For all other continuous outcomes (Table 3), we will conduct separate linear model analyses examining for any superiority of iSMT over gSMT. Group differences in newly developed Items (e.g., user preferences towards using Internet-based vs. in-person training) will be analyzed using non-parametric statistics. In addition, for all outcomes and assessment points, Cohen’s d will be calculated to quantify the size of interventional effects by subtracting the average score of the Internet-based condition from the average score of the group condition and dividing the result by the pooled standard deviations at the corresponding assessment point.

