### Recruitment and procedures

Recruitment will occur in the winter through summer of 2022, employing two major strategies. To attract interested organizations, we will use different media channels to motivate owners of small- and medium-sized companies (staff headcount < 250) in the target region to offer the intervention to their workforce. To attract individuals, health insurance companies will advertise the study via announcements in print membership magazines and media channels (e.g., Facebook, Twitter). Registration into the study will take place at an individual level, so employees need not self-disclose to their employer that they want to participate. An open-access website will provide information on study conditions. Applicants will sign up by providing an email address and name or pseudonym on the website. Applicants who fulfill all inclusion criteria assessed by an online screening questionnaire, return their informed consent, and complete the baseline assessment (T1) will receive a phone call by a research assistant to inform them about further requirements for inclusion (e.g., time scheduling for each of the interventions) and to answer the applicants’ questions. Thereafter, each applicant will be randomly allocated to one of the study conditions (Fig. 1), with randomization stratified by whether or not employees work in companies concurrently conducting organizational mental health programs. Allocation concealment will be ensured by an independent researcher not otherwise involved in this study, who will randomize study participants with a separate randomization sequence for each strata (concurrent organizational health program = yes/no). We will use a restricted randomization procedure using varying block sizes of 4 to 6 generated by the software RandList (randomization.eu). This researcher will send randomization results to the study administration responsible for subject allocation. For practical reasons, blinding of participants will not be possible.

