### Outcome measures

#### Primary outcome

The primary outcome will be the level of self-rated stress (Table 3), measured using the Perceived Stress Scale (PSS-10) [49], a validated measure of stress that has been used extensively during evaluations of both in-person and Internet-based stress-management interventions. The PSS-10 assesses the extent to which participants experience their lives as stressful (e.g., as overstraining, unmanageable, and/or unforeseeable over the past month). It consists of ten items, each having the following 5-point Likert scale response options of 0 = never; 1 = almost never; 2 = sometimes; 3 = fairly often; and 4 = very often (summation score range 0–40). In this trial, respondents will answer items referring only to the past week. The German version of the scale has been validated in the general population [50]. An online version of the German scale has also been validated in samples of German employees, exhibiting good reliability with McDonald’s omega (ω) = .89 and good measurement invariance [51].

**Table 3 Tab3:** Outcome measures and assessment points

Outcome measures	T0	T1	T2	T3	T4
Perceived Stress Scale (PSS)	✓	✓	✓	✓	✓
Center for Epidemiological Studies on Depression Scale (CES-D)	-	✓	-	✓	-
Brief Resilience Scale (BRS)	-	✓	-	✓	-
Perceived Occupational Stress (POS)	-	✓	-	✓	-
Technology Readiness (TRI 2.0)	-	✓	-	-	-
Patient Questionnaire on Therapy Expectation and Evaluation (PATHEV) – adapted for stress management training	-	✓	-	-	-
Effort-Reward-Imbalance Questionnaire (ERI)	-	✓	-	✓	-
Job Crafting Scale (JCS) - adapted	-	✓	-	✓	-
Treatment Inventory of Costs in Psychiatric Patients (TIC-P), subscale for productivity loss	-	✓	-	-	✓
Health and Labor Questionnaire (HLQ)	-	✓	-	-	✓
Assessment of Quality of Life (AQoL-6D)	-	✓	-	-	✓
Client Satisfaction Questionnaire (CSQ/CSQ-I)	-	-	-	✓	-
Preferences for online and group stress management - self-developed	-	✓	-	✓	-
Adherence to the intervention - self-developed	-	-	-	✓	-
Beck Depression Inventory (BDI), suicide ideation item	✓	-	-	-	-
Socio-economic variables (staff headcount, including income from paid employment, history of health service use, current health-related change programs in the organization, preference for Internet-based vs. in-person group training for stress reduction)	✓	-	-	-	-

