### Primary outcome analysis

Referring to the CONSORT guidelines for non-inferiority trials [27], our analysis of non-inferiority will be limited to participants who adhere to the study protocol (per-protocol analysis). That means we will only include participants who have been randomly allocated, have complete data, and attended at least five out of seven iSMT or gSMT sessions. To declare non-inferiority, the upper bound of the 95% confidence interval (CI) for the difference in mean scores on the PSS between iSMT and gSMT must be below the margin ∆. For non-inferiority, we also will conduct a separate analysis based on an intention-to-treat (ITT) sample, including all randomly-allocated subjects, to test for iSMT superiority with a one-sided alpha error set at α = .05. This procedure has been found appropriate for non-inferiority evaluations [27, 70]. For analysis of the primary outcome, we will use linear models adjusted for the baseline outcome value and stratification variable. The primary outcome will be perceived stress at T3.

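### The responder comparison uses an unadjusted Pearson chi-square although baseline PSS is a moderate predictor of response and the primary model already adjusts for it: valid, but modestly inefficient (low priority)

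*Protocol article*

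**What the plan says.** - **Secondary outcome analyses (protocol article):** a participant counts as reliably improved if the PSS-10 falls from T1 to T3 "with a reliable change index greater than 1.96, which equals 5.8 points on the PSS-10". The two arms are then compared as follows: "Response rates will be analyzed using the Pearson χ2 statistic". No covariate is named. The section describes its content as explorative: "we will conduct a variety of explorative analyses on secondary outcomes".
- **Primary outcome analysis:** for PSS at T3, "we will use linear models adjusted for the baseline outcome value and stratification variable".
- **Recruitment and procedures:** allocation is restricted "with randomization stratified by whether or not employees work in companies concurrently conducting organizational mental health programs". Baseline PSS is not a stratification factor.
- **Participants:** no PSS threshold is among the entry criteria.

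**The concern.** Response here is a change score cut at a fixed point. Someone who happens to score high at T1 is more likely to show a large fall by T3, through regression to the mean alone. T1 PSS therefore carries information about who responds, whichever arm they are in. It is not balanced by design, and no entry threshold narrows its spread.

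The article recognises this for the mean PSS at T3 and adjusts for baseline and stratum. For the dichotomised form of the same measurements it names a test that can use neither term, and gives no reason. At stake are the width of the interval around the responder difference and the way a chance baseline difference between arms feeds into that estimate.

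**Working it through.** **1. The plan's own figures**

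- Reliable-change threshold = 1.96 × SD × √2 × √(1 − reliability). The SD is 6.3 (Secondary outcome analyses) and omega is 0.89 (Primary outcome). The result is 1.96 × 6.3 × 1.4142 × √0.11 = 5.79, so the stated 5.8 is reproduced. PSS scores are whole numbers, so response means a fall of 6 or more.
- Sample size: margin 2, SD 6.3, two-sided α 0.05, 80% power. A t-based calculation gives 157 per arm, 314 in total, as stated. The check below uses 157 per arm.

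**2. Does the floor of the scale rule people out?**

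Only a T1 score below 6 makes response impossible. The share is Φ((5.5 − mean)/6.3): about 0.4% at a T1 mean of 22, 1% at 20 and 5% at 16. These means are assumptions. The floor matters little.

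**3. How well does T1 PSS predict response?**

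With equal SDs at T1 and T3 and correlation ρ, baseline explains (1 − ρ)/2 of the variance of the change score: 35%, 25% or 15% for ρ = 0.3, 0.5 or 0.7. After cutting at 6 points less remains: simulation gives about 0.24 down to 0.10 of responder variance.

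**4. What does adjustment gain?**

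Simulation: 157 per arm, SD 6.3, PSS rounded and limited to 0–40, 1,500 replicates per setting. Assumed, because the documents do not give them: ρ = 0.3, 0.5 or 0.7; T1 mean 16 or 22; a mean fall of 4.6 points (the article gives 4.6 as an effect against waiting list); and an arm difference of 0 or 2 points. The chi-square was compared with logistic regression on arm and T1 PSS. From that fit a standardised risk difference was formed: predict every participant under each condition, average, subtract. The stratification variable was not simulated.

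| ρ | AUC of T1 PSS | Mean SE, unadjusted | Mean SE, adjusted | Power for a 2-point difference, chi-square → logistic |
|---|---|---|---|---|
| 0.3 | 0.77–0.78 | 0.056 | 0.049 | 0.46–0.49 → 0.58 |
| 0.5 | 0.73–0.74 | 0.056 | 0.051 | 0.57–0.60 → 0.66–0.68 |
| 0.7 | 0.67–0.69 | 0.056 | 0.052–0.053 | 0.78–0.81 → 0.83–0.85 |

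- Variance of the estimate falls by 20–26%, 13–19% and 7–12% respectively. Power rises by about 4 to 11 percentage points.
- From step 3, the SE ratio is √(1 − R²): √0.90 = 0.95 and √0.76 = 0.87, a cut of about 5% to 13%.
- With no arm difference, the chi-square rejects in 3.7% to 4.9% of replicates against a nominal 5%.

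**5. What does a chance baseline difference do?**

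The SE of the difference in mean T1 PSS is 6.3 × √(2/157) = 0.71 points. A baseline difference δ moves the difference in mean change by (1 − ρ)δ. The unadjusted risk difference moves by φ(0.9/s)/s × (1 − ρ)δ, where s = 6.3 × √(2(1 − ρ)) and 0.9 = 5.5 − 4.6. For ρ = 0.5, s = 6.3 and a one-SE imbalance gives 0.395/6.3 × 0.5 × 0.71 = 0.022. Over ρ = 0.7 to 0.3, one SE of imbalance moves the estimate by 1.7 to 2.6 percentage points and 1.96 SE by 3.4 to 5.2, against an SE of the risk difference of about 5.6 points.

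**The case against.** The strongest reply is that nothing here is wrong. Under randomisation the chi-square holds its error rate, and chance imbalance is already part of its sampling variation. The endpoint is an explorative, participant-level complement to the primary model, which does adjust. Two raw proportions are also easier to read than a standardised estimate. All of this stands. It means that lost precision and chance imbalance are two views of one modest loss, not two defects.

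It does not remove the point. The article names the test, so this is a stated choice rather than detail left to an analysis plan. Both covariates are already collected, and adjustment gained precision in every setting tried.

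A reader might infer more than the documents support:

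- **That baseline PSS largely determines who can respond.** The floor excludes few people, and baseline explains only about 10% to 24% of responder variance.
- **That the chi-square is biased or invalid.** Its simulated type I error does not exceed 5%.
- **That the choice carries into the cost-effectiveness analysis.** Under Economic evaluations, that analysis counts reliable improvements at T4 and uses bootstrapping. It shares the responder definition, not this test.
- **That the test cannot cope with the expected 30% dropout.** How missing outcomes are classified is separate from the test, and an article commonly leaves that detail to the fuller plan.

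**Conclusion.** The point holds as a minor matter of efficiency and consistency. Adjusting for T1 PSS would cut the SE of the responder risk difference by about 5% (ρ = 0.7) to 13% (ρ = 0.3). Put the other way, the unadjusted SE is about 1/0.95 = 1.05 to 1/0.87 = 1.15 times the adjusted one. Adjustment would also remove most of the effect of a chance baseline difference.

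The size rests on a T1–T3 correlation and T1 mean that the documents do not give, on SD 6.3 at both times, and on a mean fall of 4.6 points. The direction does not depend on where in that range the truth lies. The non-inferiority conclusion does not use this endpoint, so the priority is low.

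**What to change.** Replace the chi-square as the main responder analysis with a logistic regression of reliable improvement at T3 on condition, T1 PSS and the stratification variable. Report the standardised (marginal) risk difference, iSMT minus gSMT, with a 95% CI. The interval also guards against reading a non-significant difference as equal benefit, an inference the article's Background calls premature for earlier trials. Keep the raw proportions and the Pearson chi-square as a descriptive check.

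The cost is a change of wording before the data are analysed. No new data are needed, since PSS at T1 and T3 and the stratum are already recorded. The small price is one more modelling step and a less immediately transparent main estimate, which the raw proportions alongside it offset.

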### Economic evaluations

We will perform economic evaluations from different perspectives. From an employer’s perspective, we will conduct cost-benefit analysis (CBA), considering opportunity costs due to the time required for employees to partake of the intervention and changes in productivity loss due to reduced absenteeism and presenteeism. Since health insurance companies in several countries are legally obligated to fund preventative actions, we will conduct a separate CBA from an insurer’s perspective, including intervention costs, reflected as the common market prices for the interventions. In addition, we will conduct cost-effectiveness analysis (CEA). For the CEA, we will calculate intervention costs and costs due to productivity loss and effects of the interventions, in terms of the number of reliable improvements in perceived stress at T4. The costs and effects of both interventions will then be combined in an incremental cost-effectiveness ratio [28]. A non-parametric boot-strapping method with 95% confidence intervals will be used to account for the uncertainty of differences between the two intervention groups. Finally, we will determine the probability that the intervention is cost effective for different values of willingness-to-pay per effect unit.

### Moderator analyses

Furthermore, we will explore different moderators that might affect the comparative efficacy of iSMT vs. gSMT: patient age, gender, training experiences, technology readiness, training expectations, preferences towards in-person group- or Internet-based training, working conditions in terms of an effort-reward-imbalance, and job crafting. To explore whether any of these characteristics moderate either intervention’s effect, we will conduct separate analyses. For each potential moderator, we will add to the statistical model the potential moderator as the main effect, as well as the interaction effect between the moderator and study condition on the primary outcome.

## Discussion

The currently planned study aims to examine for non-inferiority of a guided, Internet-based stress management training (iSMT) program, relative to an established, in-person group-based, stress management training (gSMT) program, in terms of their effectiveness reducing stress in employees. To the best of our knowledge, this is the first non-inferiority trial comparing the relatively new iSMT format versus an established SMT format. Findings from the present trial will broaden evidence on SMTs in several ways.

First, there is broad evidence supporting the efficacy of both traditional occupational stress management (i.e., in-person gSMT) [9, 10, 13] and iSMT [19–22] in employees. However, data comparing the efficacy of this digital training format against an established format of stress management are limited. Previous studies performing direct comparisons [25, 26] were either not powered to demonstrate iSMT non-inferiority or equivalence, relative to gSMT, or identified no improvement with iSMT [26]. Likewise, in the field of psychotherapy, meta-analyses directly comparing these two formats revealed comparable effects on psychiatric symptomology with Internet-based and established face-to-face psychotherapy [71, 72]. Although some authors are optimistic about the comparable effect sizes of Internet interventions and face-to-face interventions, such results should be interpreted with caution. Hardly any prior study was designed to directly investigate non-inferiority or equivalence employing state-of-the-art methodology [27]. Most importantly, it seems unclear if the face-to-face comparator represents the gold-standard intervention recommended by respective national guidelines. For example, in a German-speaking sample [73], eight sessions of group therapy for depression served as a comparator. However, in Germany, outpatient therapy for depression is usually individual therapy, with a minimum of 25 sessions for CBT. Therefore, previous studies may be biased, by design, in favor of digital interventions, leading to false conclusions and offering people less-effective interventions. To overcome those shortcomings, in the present trial we will use an evidence-based and widely-applied group stress management intervention in Germany as a gold-standard comparator.

Second, the trial will conduct economic analyses comparing two stress-management formats. This is of importance for employers and policy-makers seeking to adapt strategies for occupational healthcare. Especially at small- to medium-sized companies, resources for occupational health are often limited; consequently, it is important to allocate financial resources as efficiently as possible [28]. To the best of our knowledge, this is the first trial to include an economic comparison between an Internet-based stress-management intervention and a group intervention.

Third, although non-inferiority is assumed, certain subgroups might benefit more from one stress management training format versus the other. For gSMT [10] and for iSMT [19, 20], different intervention- and person-related moderators of the intervention have already been studied. In the present trial, we will explore a variety of moderators that may guide future practices and research on selective indications for either iSMT or gSMT. The identification of format-specific moderators (e.g., preferences towards one format over another) could help employers and health service providers to offer suitable interventions for specific target groups. Likewise, person-related moderators, like technology readiness, may provide important information about the basic requirements needed before successful implementation of new technology.

In the case of non-inferiority, Internet-based stress management training is complementary to established, in-person group training in occupational settings. Furthermore, if participants in iSMT experience additional benefits from this format, relative to gSMT (e.g., in terms of cost-effectiveness, availability, flexibility of use in terms of time and/or place, other aspects of convenience), iSMT would be a promising solution, especially for those companies with few resources for occupational health promotion.

### Study limitations

Despite the potential contributions of the present study, several limitations must be considered. First, participants allocated to the Internet-based condition will be offered immediate access to the online intervention, whereas participants assigned to the in-person intervention will have to wait some time before their first workshop session. Although we will make efforts to hold the workshops promptly and to schedule these training workshops as soon as possible, we expect that people in this intervention group will start considerably later than those assigned to the Internet-based treatment group. This said, this difference between these two interventions reflects the real-life characteristics of the two training formats and contribute to the study’s external validity. Second, group allocation cannot consider participant preferences, which limits conclusions regarding the implementation and actual reach of the two formats in the general employee population [74, 75]. Due to the randomized trial design, it is difficult to compare the attractiveness of the two interventions, in terms of uptake rates. Consequently, whether the Internet-based intervention shows non-inferiority or even superiority over group-based training, it remains unclear which training format would reach more employed individuals and make a greater contribution to stress reduction in the population. In psychotherapy, surveys suggest that people prefer traditional over digital care [76], but little is known about employees’ preferences regarding SMT. To address these issues, we will measure participants’ preferences towards the two intervention formats. Insights from this trial will provide a basis for allocating resources to iSMT or gSMT and facilitate future studies offering participants the opportunity to choose their preferred format. Third, digitalization of the intervention format (Internet-based vs. in-person) may be the most obvious distinctive feature of the two interventions in the present study. However, the interventions differ in several other characteristics, like the social context (individual-based vs. group-based training), major coping strategies used (problem solving plus emotional regulation techniques vs. problem solving plus cognitive restructuring), and mode of communication (asynchronous vs. synchronous). Therefore, findings from this trial cannot be attributed solely to one interventional feature. Nonetheless, the two interventions have in common that they have already been evaluated in randomized controlled trials, are offered widely in routine practice nationally, are considered gold-standard programs for either iSMT or gSMT, and offer real-life scenarios for the delivery of Internet-based and traditional healthcare programs for stress prevention [77]. Finally, participants will experience stress elicited by a great variety of work-related stressors. The Effort-Reward-Imbalance Questionnaire as a short measure for work-related stressors is unlikely to provide a multidimensional picture of the workplace situation according to, for example, the Health and Safety Executive Management Standards [78]. This would require more detailed and substantially longer assessments. However, identifying the sources of stress in detail is a complex task and require elaborated epidemiological research that is hardly feasible to conduct alongside an intervention study.
